**Inclusion criteria**	
- A suboptimal daytime SBP of > 135–160 mmHg on a 24-h ambulatory blood pressure monitoring	
- No regular physical activity or less than that recommended for adults by the World Health Organization (< 150 min of moderate-intensity aerobic exercise per week)	
- On stable doses of anti-HT medication(s) for ≥ 4 weeks if the patient is receiving drug treatments	
- Agree for no drug changes during the intervention period (24 weeks)	
- Aged ≥ 18 years old	
**Exclusion criteria**	
-Cannot provide informed consent	
-Unwillingness to repeat ambulatory blood pressure monitoring (primary outcome)	
-Relative contraindications to ambulatory blood pressure monitoring (i.e. diagnosed atrial fibrillation, nighttime workers, occupational drivers, or patients with bleeding tendencies)	
-Severe osteoarthritis pending knee replacement surgery (these patients may be unable to perform the IRE (i.e. wall squat exercise))	
-Known secondary hypertension	
-Use of ≥ 3 anti-hypertensive medications at maximum doses or ≥ 4 anti-hypertensive medications (these patients have resistant hypertension and represent another disease spectrum)	
-Systolic blood pressure or diastolic blood pressure are > 160 mmHg or > 100 mmHg, respectively, on ambulatory blood pressure monitoring at *baseline or at 12 weeks follow-up to ensure safety* (these patients require early treatment)	
-Pregnancy/breastfeeding	
-Active malignancy	

### Eligibility criteria for sites and those delivering interventions {14b}

Exercise techniques will be taught prior to beginning the program after randomization. Both initial exercise training and outcome data collection will take place at the Lek Yuen Family medicine clinic (FMC) located in Shatin, Hong Kong only. After that, participants will be remotely monitored as they perform home-based wall squat exercises or passive static stretching, according to their randomized group.

### Who will take informed consent? {32a}

Following the eligibility screening, written informed consent will be obtained by trained research assistants.

### Additional consent provisions for collection and use of participant data and biological specimens {32b}

Participants will be asked to provide optional consent for the storage of the spot urine sample at CU-Med Biobank for future studies.

## Intervention and comparator

### Intervention and comparator description {15a}

#### Intervention arm: remotely monitored home-based self-learnt wall squat exercise

Each exercise session will contain 4 sets of 2-min wall squat isometric holds with 2 min of rest between each set (approximately 14 min per session in total), and a total of 3 sessions will be arranged every week (with ideally 48 h between exercises); this is the most commonly used and most researched structure that has been shown to reduce BP [4, 5]. Our 24-week program is the longest among existing RCTs (mean = 9.8 weeks) [4]. While the longest study of wall squat, lasting a year, it included only 24 patients and did not use ABPM [26]. Although previous studies used an incremental isometric wall squat test to determine exercise intensity (i.e., knee angle during the exercise) for each patient, this is labor intensive and not feasible for routine clinical practice and large RCTs [9, 27]. It will, therefore, reduce the external validity of our study for clinical implementation. Conversely, our co-investigators, [name] and [name], used an alternative standardized algorithm to stratify patients to one of two starting joint angles, followed by standardized progression of intensity (reduction in joint angle) every 2–3 weeks. They found a similar SBP reduction at 12 weeks using this algorithm (i.e., 12.9 mmHg), an improvement comparable with other studies using initial incremental tests in non-medicated patients with HT [28]. Furthermore, the standardized algorithm had excellent patient acceptability, with no dropouts and 100% attendance in the wall squat group [28] (Table 2). A slightly modified version of this algorithm will be used in the current RCT by incorporating the validated rating of perceived exertion scale, which allowing individualized exercise progression towards 95° by 10 weeks (the maximum possible intensity) (Tables 2 and 3) [29]. This allows more capable patients to progress early if the exercise intensity is inadequate (i.e., recurrent rating of perceived exertion of < 4) [29]. This approach aims to balance the individualization of exercise intensity progression and the need to deliver an adequate stimulus while considering the patient’s comfort, motivation, and safety. Wall squat exercise techniques and the use of rating of perceived exertion will be taught prior to beginning the program. This includes the algorithm in Table 2 (i.e., progressive knee angles) and posture (feet are shoulder width apart, back and head in a neutral position/against the wall). This will be reinforced by written materials and a video (which times the exercise and reminds the patient of exercise techniques). Patients will be asked to videotape themselves performing the wall squat at the 2nd or 3rd week. They will send this to the investigators via a messaging app (e.g., WhatsApp) who will review to identify and where appropriate, correct error in execution of the exercise.

**Table 2 Tab2:** Prescription of wall squat to participants

Baseline	Can wall squat at 95’ for 2 min*	Cannot squat at 95’ for 2 min
Week 1	125’	135’
Week 2	125’ (115’)	135’ (125’)
Week 3	125’ (115’)	125’ (115’)
Week 4	115’ (105’)	125’ (115’)
Week 5–6	115’ (105’)	115’ (105’)
Week 7–9	105’ (95’)	105’ (95’)
> Week 10	95’	95’

^*^If the patient has rating of perceived exertion of < 4 at end of 2 consecutive sessions, they can increase the intensity of the exercise early as shown in the ()

**Table 3 Tab3:** Validated rating of perceived exertion

Rating	Description	Time to failure
0	Rest	100%
1	Extremely easy	90%
2	Very easy	80%
3	Easy	70%
4	Somewhat easy	60%
5	Moderate	50%
6	Somewhat hard	40%
7	Hard	30%
8	Very hard	20%
9	Extremely hard	10%
10	Maximal	0%

Adherence to exercise and physical activity level will be monitored using a smart watch, which will record exercise type and duration and the heart rate during the isometric exercises. Data from the smart watch will be examined by the research assistant weekly and patients will be contacted if the session of that are missed. Furthermore, as there will be change of knee angle every 1–2 weeks, the assistant will check the knee angle and safety at least every 2 weeks via patients’ preferred messaging app (e.g., WhatsApp) and answer any questions they might have. The patient will be asked standardized questions (e.g., “Using the perceived exertion scale, what’s the difficulty level on your last weeks’ wall squat?”, “Is there any problem performing the exercise, including discomfort or injury?”, “What is the knee angle that you will be using in the coming week?”). Participants will be asked to refrain from beginning new exercises (i.e., those not part of their prior usual habits) during the 24-week study period. Although the intervention has been well accepted by patients with HT in our previous research [28], we also successfully conducted another pilot study in 12 Chinese patients with HT from August to November 2022 using an abbreviated version of this exercise program (8 weeks instead of 24 weeks) to evaluate feasibility. We found that repeated ABPMs are acceptable to patients and there was > 87% can fully adhere to the exercise program. No adverse event was reported by patients.

#### Control arm: stretching exercise

Although stretching exercise was used in another IRT RCTs (NCT03896334), there was no widely validated sham control for wall squat in RCTs. Previous meta-analysis found that passive static stretching exercises did not change BP level in most RCTs and therefore can be active control in this RCT [22]. A frequency-matched (3 ×/week) and time-matched (~ 14 min each session) passive static stretching exercise will be used (a sample in the additional document 2 based on previous RCT using stretching and had no hypotensive effects) and taught to patients prior to beginning the program (with video support as in IRT group). The treatment in the control group, such as the research assistant’s contact, the use of smart watch and monitoring of adherence, will be the same as in the intervention group. This approach was suggested by our reviewers last year to control for hypotensive effects due to frequent contact by the research team and feedback from the smart watch in the IRT group.

#### Criteria for discontinuing or modifying allocated intervention/comparator {15b}

Participants are encouraged to adhere to their assigned allocation as closely as possible. However, if they experience serious illnesses (e.g., a traffic accident resulting in limb loss or severe infections that immobilize them) that prevent them from performing the prescribed exercises (such as wall squats or stretching), the exercises will be discontinued. We will encourage these participants to provide outcome data as far as possible. Participants also have the option to withdraw from the study at any time.

#### Strategies to improve adherence to intervention/comparator {15c}

To encourage participants to maintain their intervention habits, the research assistant will review the exercise diary weekly to bi-weekly and contact participants if their exercise frequency is insufficient during the 24-week intervention period. After this initial phase, the diary will be checked monthly, and the research assistant will contact participants if their exercise remains inadequate, until the final data collection at 12 months.

#### Concomitant care permitted or prohibited during the trial {15d}

While medical consultations and intake of medication are allowed, change in hypertensive medications should be avoided as far as possible during the 24-week intervention period.

#### Harms {17}

There are no anticipated risks associated with the wall squat and stretching exercises, as these interventions have been found to be safe, and adverse events are rare [4]. However, if any suspected or actual complications arise, participants are instructed to seek medical assistance, including attending the accident and emergency unit (access is not limited by current trial), and to contact the study team at their earliest convenience. As part of adherence monitoring, all participants already have the contact information for the research team. Any hospitalizations will be promptly reported to the relevant ethics committee within 24 h, or as soon as possible.

#### Ancillary and post-trial care {34}

Although no additional ancillary or post-trial care will be provided by the research team, the trial is designed to help participants in both the intervention and control groups establish new exercise habits. These habits may lead to sustainable, home-based exercise routines that can be maintained after the intervention. Otherwise, all participants will continue their follow-up with their usual health service providers. Clinical trial insurance has been purchased to cover compensation for any participants who experience harm as a consequence of participation in this study.

#### Participant timeline {18}

The schedule of enrolment, interventions, and assessments is summarized in Fig. 1.

#### Sample size {19}

Table 4 demonstrates the required sample sizes to identify a true difference in SBP reduction between the two intervention groups, with various assumptions on the true difference and type I error (beta). Type II error is fixed at 0.05. Based on previous reviews, SBP reduction by IRT ranged from approximately 3 to 8 mmHg [5]. A change of 3 mmHg is considered minimal clinically meaningful effect [30]. We therefore use the most conservative SBP difference of 3 mmHg between the 2 arms, and use a standard deviation of approximately 10 mmHg (on ABPM), which is typical in the HT population and confirmed in our previous local studies [10]. Targeting a statistical power of 0.8 and assuming a dropout rate of 10%, we are aiming to recruit a total of 390 participants, with 195 participants in each group [9]. This sample size is adequate if the true BP difference is 4 mmHg and at a power of 0.9 (Table 4).

**Table 4 Tab4:** Required sample size

Power (1-beta)	True mean reduction in SBP reduction between intervention groups (Intervention-Control group)*			
	3 mmHg	4 mmHg	5 mmHg	6 mmHg
0.80	175	99	63	44
0.85	200	113	72	50
0.90	234	132	85	59

^*^The required sample size is based on the targeted type I error (beta) and assumed true mean reduction in SBP between treatment groups while type II error is fixed at 0.05

#### Recruitment {20}

The research team has developed strategies to ensure adequate enrollment and achieve the target sample size. For instance, the recruitment rate will be regularly monitored monthly. Using newspaper advertisements will already ensure that our recruitment reach participants across the entire territory of Hong Kong.

## Assignment of interventions: randomization

### Sequence generation: who will generate the sequence {21a}

The randomization sequence will be generated by an independent statistician, using the statistic program “Random Allocation Software,” version 1.1.0.

### Sequence generation: type of randomization {21b}

Despite yet conclusive, a systematic review suggests that age and anti-HT drug treatments may affect response to IRT [31]. As sex-specific difference in HT is increasingly emphasized and investigated, sex is considered an important factor in stratification randomization [32]. Therefore, stratified randomization with a randomized block size of 4 or 6 will be utilized according to age (< 45, 45– < 60, and ≥ 60 years old [a cut-off used in the above review]), sex, and anti-HT drug use (users versus non-users).

### Allocation concealment mechanism {22} and implementation {23}

The randomization sequence will be printed out, and sealed in sequential and light-opaque envelopes, which will only be opened after a participant’s consent form is signed. The envelops will be kept in a closed locker to which only research assistants will have access. The envelopes will only be opened by participants after written informed consent is obtained by research assistants. The envelopes will then be filed in participant’s folder.

## Assignment of interventions: blinding

### Who will be blinded {24a}, how will be blinding be achieved {24b}, and procedure for unblinding if needed {24c}

Blinding of participants is not possible after randomization owing to the nature of the intervention. However, the investigator, outcome assessor(s), and statistician will be blinded.

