**Methods:**

This randomized controlled trial (RCT) will involve 390 patients with a suboptimal daytime systolic BP of > 135–160 mmHg on a 24-h ABPM, who do not meet the current World Health Organization recommendations for physical activity. Participants will be randomly assigned to either the IRT (wall squat) group or stretching exercise (active control) group (1:1), using stratified and blocked randomization according to age (< 45, 45– < 60, and ≥ 60 years old), sex, and anti-hypertensive drug use (users versus non-users). Investigators will be blinded to randomization sequence and allocation. IRT group will receive a well-structured, widely accepted, and validated 24-week wall squat program (2 min per exercise, 2 min of rest between sets, and 3 sessions per week). Adherence will be monitored by regular patient communication via social media. The control group will receive the same treatment, with the exercise replaced by frequency-matched and time-matched stretching exercise. The primary outcome measure will be systolic daytime ABPM at 24 weeks. Secondary outcome measures will include other BP and ABPM parameters at 12 weeks, 24 weeks, and 12 months, carotid-femoral pulse wave velocity at 24 weeks and 12 months, and flow-mediated dilation at 24 weeks and 12 months. Safety data will be collected and reported.

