## Outcomes, data collection, and management

### Outcomes {16}, plans for assessment, and collection of outcomes {25a}

After data collection at baseline, participants will return for outcome assessments at 12 weeks, 24 weeks, and 12 months. Details of the time point for outcomes and trial instruments are specified in each outcome below. All research assistants who are involved in data collection will be trained the correct use of instruments (e.g., ABPM) and questionnaires, as well as retrieval of data. After each assessment, the files will be reviewed to identify missing or erroneous data. Any missing information will be retrieved immediately from the instruments and the study participants.

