### Frequency and plans for auditing trial conduct {29}

Research team will hold monthly meeting on discussing the recruitment progress, demographic balances between two arms, data collection, and adverse events. Financial auditing of the current study will be performed by the Chinese University of Hong Kong SAR.

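### Investigator blinding is contradicted by the video review, adverse events elicited during monitoring are not blinded, and assessor blinding for other research-assistant outcomes is claimed but not secured

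*Protocol article*

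**What the plan says.** The blinding section (items 24a to 24c) accepts that participants cannot be blinded and continues: "However, the investigator, outcome assessor(s), and statistician will be blinded". The Methods part of the abstract says: "Investigators will be blinded to randomization sequence and allocation".

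Other sections describe who sees what:

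- **Video review (intervention arm).** "Patients will be asked to videotape themselves performing the wall squat at the 2nd or 3rd week". The next sentence reads: "They will send this to the investigators via a messaging app (e.g., WhatsApp) who will review to identify", and the reviewers correct errors in technique where needed.
- **Monitoring (text after Table 3).** The research assistant examines smart-watch data weekly, and these data include the type of exercise. In addition, "the assistant will check the knee angle and safety at least every 2 weeks". The example questions for this contact cover exertion, discomfort or injury, and the knee angle for the coming week. The control-arm section gives controls the same contact and monitoring.
- **Adherence strategies (15c).** The research assistant reviews the exercise diary through the 24 weeks and then monthly until the 12-month data collection.
- **Envelopes (22, 23).** Only research assistants have access to the locker. Participants open their envelope after a research assistant has obtained consent. "The envelopes will then be filed in participant’s folder".
- **Outcome collection (25a).** "All research assistants who are involved in data collection will be trained the correct use of instruments (e.g., ABPM) and questionnaires".
- **FMD.** A senior sonographer, described as blinded, makes these measurements.

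**The concern.** The protocol makes a positive claim about three roles and then gives at least one of them a task that cannot be done blind. The background section criticises most earlier trials for flaws in assessor blinding and allocation concealment, so staff blinding is one of the advantages this trial claims. Participants know their arm, which leaves staff blinding as the main remaining protection against differential assessment.

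Two things are at stake. First, a trial report that repeated the abstract and the blinding section would misstate how the trial was run. Second, some outcomes depend on the person collecting them. Adverse events, falls and musculoskeletal injuries are partly self-reported, and the proportions with adverse effects are compared between arms by chi-square test. cfPWV is measured by applanation tonometry, and its operator is not named.

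**Working it through.** The blinding claim contains no figure, and the sample size does not depend on it, so the check sets the sections against one another role by role.

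1. **Investigators.** Claim: blinded to allocation (abstract; 24a). Procedure: the investigators receive and correct a video of the wall squat. Only the intervention arm does wall squats, so the video identifies the arm. No reading keeps the reviewer of a video blinded to that participant. *Contradicted.*

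2. **Adverse events elicited during monitoring.** Claim: outcome assessors are blinded. Procedure: one assistant asks about knee angle and about discomfort or injury in the same contact, and reviews watch data showing exercise type. Controls have equivalent contact. The patient safety section has falls, injuries and other events partly self-reported and monitored throughout the trial. The person hearing these reports during follow-up therefore knows the arm. *Blinding absent for this route.*

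3. **ABPM fitting and questionnaires.** Claim: assessors are blinded. Procedure: research assistants are the job group that controls the envelopes, monitors the exercise and collects outcomes, and the opened envelope is stored in the participant's folder. No section separates monitoring staff from assessing staff or says how the folder is kept from assessors. Equally, no section says that the same individual does both. *Asserted, not secured.*

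4. **cfPWV.** The operator is not named. If it is a research assistant, step 3 applies; if not, the document does not show. *Possibly not secured.*

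5. **FMD.** A separate sonographer is stated to be blinded, and no procedure reveals allocation to that person. *Not contradicted.*

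6. **Statistician.** No described procedure reveals allocation to the analysing statistician. *Not contradicted.*

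**Exposure of the primary endpoint.** Daytime SBP is an average of automated readings, and the definition of a valid recording follows a published guideline. Limited discretion remains: waking-hours-only recording for reluctant participants, sleep times taken from a diary, and retrieval of missing information. Bias here is probably small.

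**Scope for change.** The trial status section gives 190 of 390 recruited. 390 − 190 = 200 participants were still to enrol at that point, and follow-up visits remained for those already in.

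**The case against.** The strongest reply is that only the video conflict is explicit and the rest is inference from a condensed article. The wording on data collection can be read as describing a separate group of research assistants, and monitoring is assigned to a single assistant. Delegation of duties is commonly left to the full protocol. The consequences are also limited. The primary outcome is automated, the questionnaires are covariates that participants answer themselves, adverse events are also retrieved from the computerised medical record, and secondary analyses are labelled exploratory.

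Much of this stands, and it limits the point. Several stronger readings are tempting, but the document does not support them:

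- *That allocation is revealed to all outcome assessors, so that no blinding exists.* The text does not show that the same person monitors and assesses, and blinding of the sonographer and the statistician is untouched.
- *That assessors see the allocation at every visit.* The envelope is filed in the folder, but the folder is not said to be used at visits.
- *That every wall-squat participant is unblinded to an investigator by week 3.* Participants are asked to send a video; full compliance is not stated.
- *That the monthly team meeting breaks the blind.* Its review of demographic balance could be done on coded arms, and group-level balance does not disclose an individual's allocation.

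The reply does not remove the first two steps of the check. The video goes to a role that is declared blinded, and the question about injury is asked by someone who is discussing the knee angle. Record retrieval reduces reliance on that conversation, but the self-reported route remains.

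**Conclusion.** The concern holds in a limited form. Investigator blinding is contradicted by the protocol's own procedure. Blinding is absent for adverse events elicited in the monitoring contacts. For ABPM fitting, questionnaires and possibly cfPWV, assessor blinding is claimed without being secured, and whether it fails in practice depends on staffing that the article does not describe. FMD and statistician blinding stand as stated.

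The likely effect on the primary endpoint is small, on the assumption that automated readings and guideline validity rules leave staff little influence. The size for cfPWV and self-reported events cannot be derived from the document. Even if duties are already divided in practice, the abstract, the blinding section and the intervention description still need to be reconciled.

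**What to change.** 1. Route the videos and all exercise messaging to designated existing staff who are declared unblinded and who do not assess outcomes for the same participant.
2. File opened envelopes in a separate allocation file that assessors cannot access, instead of the participant's folder.
3. Restate the abstract and the blinding section so that they list only those actually blinded. Say that staff who review videos and elicit adverse events during monitoring are not blinded, and that this applies to participants already enrolled.

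The cost is a reallocation of duties, one extra file and a few sentences; the sample size, endpoints and analysis do not change. The downsides are less flexible staffing, which may be tight because the article gives no number of assistants, and a less favourable blinding statement. Restricting the monthly meeting to pooled data is not advised: it would remove the planned balance check and any arm-level look at adverse events in a trial with no data monitoring committee.
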